### 2.7. Secondary Outcomes

Apgar scores and delivery room resuscitation including the requirement for endotracheal intubation.Core axillary temperature (digital electronic thermometer) at 5 min of age and on admission to NICU.Respiratory support including surfactant, length and type of support.Transitional circulation assessed based on blood pressure recorded from arterial lines where possible or peripheral recordings if no arterial lines, acid base, lactate, echocardiogram performed within first 6–12 h if possible, inotropes received (first 48 h) and patent ductus arteriosus treatment rates during neonatal admission.Phototherapy received (requirement based on local guidelines) haemoglobin levels on days 1 at 24 h of age and days 2, 3 and 7 (from capillary or venous FBC as preference or capillary gas).Neonatal outcomes as defined by local neonatal network coding criteria [28]. These include: chronic lung disease (CLD) defined as respiratory support or oxygen received at 36 weeks corrected gestational age, discharge home with oxygen, intraventricular haemorrhage (IVH) rates (grades III and IV and any grade reported) within first 24 h if possible, day 5 and day 28 cranial ultrasound, necrotising enterocolitis (NEC) defined by modified Bells stage 2 or higher, retinopathy of prematurity (ROP) highest stage recorded and requiring laser therapy, early onset sepsis (EOS) < 48 h of age and late onset sepsis (LOS) defined by positive blood culture or cerebrospinal fluid after 48 h, death during neonatal admission and length of hospital stay in days [28].Neurodevelopmental outcome at 2 years of age (for infants ≤ 29 week gestation).

### 2.8. Sample Size

Data from an observational study indicated that 60% of infants that received DCC and did not breathe received a blood transfusion. This compared to 30% transfused in the group that breathed during DCC. Aiming for a similar 50% relative reduction in the proportion transfused would require 100 infants whose primary outcome could be assessed. To allow for cases where outcome assessment may not be possible (deaths, surgical transfer), 120 infants are to be randomised (60 per group). (A total of 100 would give the study 85% power at a two-sided significance level of 0.05). For a secondary composite outcome of death, CLD or severe IVH, the sample size would allow a 36% difference in outcome to be detected (80% power, significance 0.05), assuming the percentage of infants with a composite endpoint will be 58% (based on historic data).

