## 1. Introduction

Major physiologic changes occur during the transition immediately after birth. These include lung aeration and expansion, which is associated with a marked and rapid reduction in pulmonary vascular resistance and increased pulmonary blood flow [1]. This changes the direction of the ductal shunt so that it is primarily left to right, and the systemic blood flow is largely derived from the increased left ventricular output. The in utero vascular resistance is low because of the placental bed. Cord clamping has the potential to change this vascular resistance, particularly if the lungs have not been expanded [2,3]. Preterm infants, who may not rapidly establish adequate lung aeration before cord clamping, are at a high risk of perturbations to this normal process especially if the cord is clamped early. Indeed, clamping the preterm cord after a delay of at least 30 s has been shown in a number of systematic reviews to improve survival, although this finding was recently noted to be of borderline significance [4,5,6]. As noted above, however, the critical factor in the timing of the cord clamping may be related to the onset of respiration rather than the time elapsed. Whilst this was suggested years ago [7,8], there has been a recent resurgence of studies examining “physiologic” cord clamping once breathing is fully established [9,10]. To date, most of these studies are small feasibility studies, although larger clinical studies are underway or have been proposed [11]. If the cord is not clamped immediately (or “early”) and clamping is “deferred” or “delayed” (DCC) for a period of time (e.g., 30 to 60 s), many infants, including those that are very preterm, will be breathing before clamping. In a recent study of infants < 32 weeks, this amounted to approximately 70% at 30 s and 90% by 60 s [12,13]. On the other hand, if preterm infants are not breathing before clamping, they may be deemed to be in need of resuscitation, hence the term “neonatal resuscitation with an intact cord” [1].

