Although the reasons for neonatal transfusion are multifactorial, there is evidence of a transfer of blood from the placenta (a placental transfusion) to the infant in cases where DCC occurs, and this may be one mechanism for the observed reduction in neonatal transfusions. Although a few studies have directly measured the infant’s blood volume, most of the evidence for placental transfusion is indirect [16,17]. There is an increase in haematocrit in many randomised trials (where the control group did not have DCC), an increase in body weight demonstrated by continuous weighing after birth with the cord intact and a corresponding decrease in placental weight compared to cases where no DCC occurred [4,16,18]. In addition, many earlier studies measured the residual placental blood volume (RPV) by allowing blood from the placenta to drain under gravity into a graduated measuring cylinder after delivery [19], DCC was associated with a reduction in the RPV. Important factors determining the RPV, i.e., the inferred amount of placental transfusion, were whether breathing occurred during DCC and the length of time after birth before the cord was clamped. In term infants, it appeared that the initial cry was enough to facilitate placental transfusion, as the majority of the decrease in RPV occurred quickly, even if breathing was not sustained. In preterm infants, however, this placental transfusion appeared to take longer, possibly associated with a reduced respiratory effort [19,20]. In addition, the length of DCC may be curtailed because of the desire of attending staff to start early resuscitation, particularly if early respiration is not vigorous. The effect of this shorter duration of DCC combined with irregular respiration on placental transfusion is not clear. Such infants may have been excluded from randomised trials (approximately 20% in the two largest studies) [14,15]. In an observational study of infants < 30 weeks carried out at our hospital, of 46 infants undergoing DCC (40 s or more), 34 established regular breathing during the procedure, whilst 12 (26%) did not. Sixty percent of infants that received DCC and did not breathe received an RBC transfusion compared to 32% in the group that breathed regularly. The median day 1 haemoglobin was significantly higher in this latter group (*p* = 0.003). These differences suggest a larger placental transfusion in the group that breathed during DCC even though the length of DCC was similar [21]. This led us to question whether providing respiratory support to preterm infants who did not establish regular breathing during DCC (but were not otherwise compromised) would allow a greater placental transfusion to take place and subsequently reduce neonatal blood transfusion requirements. We estimated that the assessment and randomisation could be completed within 20 s of birth and planned a further 30 s of DCC, with 1:1 randomisation to either receive respiratory support or no respiratory support during the last 30 s. All study infants would receive a total of 50 s DCC. In PICOT format, this was as follows:

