## 2. ABC Study Protocol

The Assisted Breathing before Cord Clamping study (The ABC Study) (http://www.anzctr.org.au/ACTRN12615001026516.aspx, accessed on 28 January 2020) protocol is described below in more detail. The study design was a single centre randomised controlled trial at a New Zealand centre that had first implemented DCC in 2010. On average 70 < 31 weeks infants are admitted per year, and it was estimated that 50% of infants undergoing DCC would not be breathing regularly by 15 s [13].

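### The 60% control rate behind the 85% power comes from infants who never breathed during DCC, not from infants irregular at 15 s whom the trial randomises, so the power is probably overstated

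*Protocol article*

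**What the plan says.** Section 2.8 bases the primary-outcome sample size on two rates from the centre's observational study. For control: "Data from an observational study indicated that 60% of infants that received DCC and did not breathe received a blood transfusion". For the target: "This compared to 30% transfused in the group that breathed during DCC". It continues: "Aiming for a similar 50% relative reduction in the proportion transfused would require 100 infants whose primary outcome could be assessed", and gives the power as "A total of 100 would give the study 85% power at a two-sided significance level of 0.05". In all, 120 infants are to be randomised, 60 per group, to allow for losses.

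The Introduction describes the source cohort of infants below 30 weeks: "of 46 infants undergoing DCC (40 s or more), 34 established regular breathing during the procedure, whilst 12 (26%) did not". It reports the rates as follows: "Sixty percent of infants that received DCC and did not breathe received an RBC transfusion compared to 32% in the group that breathed regularly".

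Eligibility is set by a different observation. Sections 2.1, 2.3 and 2.5 randomise infants below 31 weeks whose breathing is irregular or absent at 15 s and who are not otherwise compromised. Section 2 gives the size of that group: "it was estimated that 50% of infants undergoing DCC would not be breathing regularly by 15 s". For a separate study of infants below 32 weeks, the Introduction says of the proportion breathing before clamping that "this amounted to approximately 70% at 30 s and 90% by 60 s".

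**The concern.** The 60% belongs to infants who did not breathe regularly at any point in 40 s or more of DCC. The trial enrols on a single assessment at 15 s, with the clamp at 50 s. Some control infants will start regular breathing in between without help. In the source cohort those infants would have counted as breathers, the group that supplied the 30% target. Section 2.8 makes no adjustment for this.

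The 85% is the only power statement for the primary outcome. If it is too high, a non-significant result from about 100 infants would be taken as stronger evidence against assisted breathing than the design can give.

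**Working it through.** **Method.** Two-sided 0.05, normal approximation, n per arm, p̄ the mean of the two rates:
power = Φ{ [ |p1 − p2| − 1.96·√(2p̄(1 − p̄)/n) ] / √([p1(1 − p1) + p2(1 − p2)]/n) }.

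**1. The plan's own figure.** 60% v 30%, n = 50: (0.30 − 1.96 × 0.0995)/0.0949 = 1.107, power 86.6%. Fisher's exact test gives 82.9% and an exact Pearson chi-square 87.6%. The stated 85% is right for its inputs.

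**2. The comparison rate.** 60% v 32% (Introduction), n = 50: (0.28 − 1.96 × 0.0997)/0.0957 = 0.885, power 81.2%. The relative reduction is 28/60 = 47%, not 50%.

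**3. Who is randomised.** Never-breathers are 26% of DCC infants (Introduction); infants irregular at 15 s are 50% (section 2). The share of never-breathers among those randomised is s = 0.26/0.50 = 0.52, and the other 0.48 are late breathers. This combines two sources with different gestation limits.

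**4. Control rate.** With r the transfusion rate in late breathers, which the article does not give:
control = 0.52 × 60% + 0.48 × r.
- r = 32%: 31.2 + 15.4 = 46.6%
- r = 30%: 31.2 + 14.4 = 45.6%
- r = 45%: 31.2 + 21.6 = 52.8%
- r = 60%: 60%, the planned value

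**5. Power at 50 per arm.** Each row rests on the assumption shown.

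| Assumption | Control v intervention | Power |
|---|---|---|
| Late breathers carry the breathers' rate (32%) and are not helped | 46.6% v 32% | 32% |
| The same with 30% | 45.6% v 30% | 36% |
| Late breathers carry 45%; all infants reach 32% | 52.8% v 32% | 56% |
| 46.6% control; planned 50% relative reduction kept | 46.6% v 23.3% | 69% |
| Late breathers carry 45%; all infants reach the early-breather rate | 52.8% v 25.8% | 80% |
| Late breathers carry 60% and benefit as never-breathers do | 60% v 32% or 30% | 81% or 87% |

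The 25.8% in the fifth row comes from splitting the 46 infants. Half (23) breathe by 15 s, 34 − 23 = 11 breathe late, and 12 never do. Holding the breathers' average at 32% with late breathers at 45%, the early rate is (34 × 32% − 11 × 45%)/23 = 25.8%.

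**6. If only never-breathers are helped.** The difference is then 0.52 × (60 − 32) = 14.6 points whatever r is, and power stays at about 31–32% for r from 32% to 60%.

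**7. Detectable difference.** From a 46.6% control rate, 50 per arm has 80% power for a fall to about 20.5%, which is 46.6 − 20.5 = about 26 points.

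**The case against.** The strongest reply is that nothing has been miscalculated. The 85% follows from its inputs, and the dispute is over a design assumption. That is correct, and it limits the point to the population behind the input.

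A reader might infer that the article's own figures imply about 32% power. They do not. That value needs late breathers to carry the breathers' average rate and to gain nothing from ventilation, and the article states neither. Nor is 14.6 points a ceiling. The Introduction ties placental transfusion to both breathing and time before clamping, and says that it appears to take longer in preterm infants. An infant who would have breathed late could therefore gain from support started by 20 s. On that reading the 32% is an average over better early and worse late breathers, and power of about 80% is consistent with the reported rates. Pushing it further, a late-breather rate of about 47% would reach 85%. That requires ventilated infants to do better (about 25%) than the 30% that section 2.8 itself targets.

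Two other inferences also fail. Excluding compromised infants does not show that the trial population is milder than the source group, because such infants may never have completed 40 s of DCC and so may not be among the 12. The pooled relative risk of 0.81 compares delayed with early clamping, which is a different contrast from this trial's.

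The 26% and 50% do come from different cohorts, and the third set of figures (90% breathing by 60 s) does not agree with the local 74%. This makes the 52% approximate. It does not restore the match between the 60% and the infants enrolled.

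The 30% against 32% may be rounding, but it takes the power from 87% to 81%.

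**Conclusion.** The concern holds as a mismatch of populations. The 60% describes infants without regular breathing throughout DCC, while the trial enrols on breathing at 15 s. On the article's 26% and 50%, about half of those enrolled would be never-breathers. The control rate is then about 47% if late breathers have the breathers' risk, and 60% only if they have the full never-breather risk.

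Power at 50 per arm is about 32–36%, 56%, 69% or 80% under the assumptions tabulated. If the breathers' rate of 30–32% is taken as the target, as section 2.8 does, roughly the stated power returns only when late breathers carry the full 60% and benefit equally. The article offers no support for that. The size of the overstatement cannot be fixed from the article because the late-breather rate is missing. The 60% is itself imprecise, since it rests on 12 infants (7/12 is 58%).

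**What to change.** Keep the sample size and restate section 2.8:
- Say that the 60% comes from infants who did not breathe regularly throughout DCC of 40 s or more.
- Give the expected control rate for infants irregular at 15 s as a range, about 47–60% on the assumptions above.
- Use 32% as the source figure for breathers, in line with the Introduction.
- Replace the single 85% with a power range, naming for each value the assumed late-breather rate and whether late breathers benefit.
- State what 100 assessable infants can detect with 80% power: about 26 points from a 47% control rate.

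The cost is rewording and a less favourable power statement. No extra patients are needed.

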### 2.9. Intervention Assignment

Sequence generation: One-to-one allocation to study groups based on computer generated randomisation sequences with random block sizes. Groups will be stratified into ≤26, >26 and <28 weeks and ≥28 to <31 weeks gestation.

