### 2.14. Statistics

Initial chi-square tests for categorical data. Numeric data are to be analysed with Mann–Whitney non-parametric statistics or t test if normally distributed. Secondary analysis is planned using logistic regression (IBM SPSS Statistics 26, IBM Corporation 2020, New York, NY, USA). Two-sided probability (*p* value) < 0.05 will be used to indicate statistical significance.

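### The 36% detectable difference stated for the secondary composite does not match 80% power on either the absolute or the relative scale, if 58% is the standard-care rate and testing is two-sided

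*Protocol article*

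**What the plan says.** Section 2.8 sizes the trial on the transfusion outcome, 60% against 30%, which "would require 100 infants whose primary outcome could be assessed". It adds that "A total of 100 would give the study 85% power at a two-sided significance level of 0.05". To cover infants who die or are transferred for surgery, the number is then raised: "120 infants are to be randomised (60 per group").

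The same paragraph closes with a power statement for a secondary composite of death, CLD or severe IVH. Its claim is that "the sample size would allow a 36% difference in outcome to be detected (80% power, significance 0.05"). The rate on which this rests is 58%, taken from historic data.

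Three things are left open in that last sentence: whether 36% is a difference in percentage points or a relative change, whether n is 100 or 120, and whether 58% is the rate under standard care or over both arms. Sidedness is not repeated there, but section 2.14 sets a two-sided p value below 0.05 as the criterion that "will be used to indicate statistical significance". Section 2.9 gives the allocation: "One-to-one allocation to study groups based on computer generated randomisation sequences with random block sizes".

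**The concern.** A detectable difference, a baseline rate, a power, a significance level and a sample size are tied together by one equation. Here four of them are stated or can be found in the protocol, so the fifth can be checked. A 36-point fall from 58% is very large for 50 or 60 infants per arm and should have far more than 80% power. A 36% relative fall is about 21 points and should have clearly less. The stated figure appears to lie between the two scales and to fit neither.

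The scale matters because the primary target in the same paragraph is expressed as a relative reduction, so a reader may well take the 36% as relative too. On that reading the chance of missing such an effect would be roughly 37% to 45%, where the protocol implies 20%. On the absolute reading the sentence errs the other way and understates what the trial can detect.

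**Working it through.** **Inputs.** Composite rate p1 = 0.58 (section 2.8), taken as the standard-care rate because it is described as historic. n = 50 per arm (100 assessable) or 60 per arm (120 randomised) (section 2.8). Allocation 1:1 (section 2.9). Chi-square test, two-sided 0.05 (section 2.14). Stated power 80% (section 2.8).

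**Formula.** Two proportions, pooled variance under the null hypothesis, no continuity correction:

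z_power = [ |p1 − p2| × √n − 1.96 × s0 ] / s1, and power = Φ(z_power),

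with p̄ = (p1 + p2)/2, s0 = √(2p̄(1 − p̄)), s1 = √(p1(1 − p1) + p2(1 − p2)).

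**Step 1: the protocol's own primary figure.** 0.60 v 0.30, n = 50: s0 = 0.7036, s1 = 0.6708. z_power = (0.30 × 7.071 − 1.96 × 0.7036)/0.6708 = 1.107, so power is 86.6%. The protocol states 85%. The method therefore agrees with the neighbouring statement.

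**Step 2: 36% as percentage points.** 0.58 v 0.22: s0 = 0.6928, s1 = 0.6444.
- n = 50: z_power = (0.36 × 7.071 − 1.96 × 0.6928)/0.6444 = 1.843, power 96.7%.
- n = 60: z_power = (0.36 × 7.746 − 1.96 × 0.6928)/0.6444 = 2.220, power 98.7%.
- 80% power would need only 28 per arm.

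**Step 3: 36% as a relative reduction.** p2 = 0.58 × 0.64 = 0.371; s0 = 0.7063, s1 = 0.6907.
- n = 50: z_power = (0.2088 × 7.071 − 1.96 × 0.7063)/0.6907 = 0.134, power 55.3%.
- n = 60: z_power = (0.2088 × 7.746 − 1.96 × 0.7063)/0.6907 = 0.338, power 63.2%.
- 80% power would need 89 per arm.

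**Step 4: other readings, same formula.**

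| Reading | 50 per arm | 60 per arm |
|---|---|---|
| 36% is the target rate (58% v 36%), two-sided | 59.9% | 67.9% |
| Relative increase (58% v 78.9%), two-sided | 61.6% | 69.6% |
| Relative increase (58% v 78.9%), one-sided | 73.1% | 79.9% |
| Target rate 36%, one-sided | 71.7% | 78.5% |
| Relative fall (58% v 37.1%), one-sided | 67.6% | 74.5% |
| 58% is the mean of both arms, relative fall 36% (70.7% v 45.3%), two-sided | 73.9% | 81.5% |

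For the last row, the control rate is 2 × 0.58/1.64 = 0.707 and the other arm is 0.64 × 0.707 = 0.453.

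**Step 5: what is detectable.** Solving the formula for p2 at 80% power with p1 = 0.58, two-sided 0.05:
- 60 per arm: p2 = 0.328, a fall of 25.2 points, relative 0.252/0.58 = 43%.
- 50 per arm: p2 = 0.305, a fall of 27.5 points, relative 0.275/0.58 = 47%.

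With continuity correction these become 26.8 points (46%) and 29.4 points (51%). Over the two-sided methods tried, the detectable fall stays between 25 and 29 points, or 43% and 51% relative. Neither range contains 36.

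**The case against.** The strongest reply is that the sentence never says that 58% is the control rate. If it is the rate over both arms, a 36% relative reduction has about 81% power with 60 per arm, which is essentially the stated figure. This shows that one cannot call the number wrong on every conceivable reading. It needs a standard-care rate near 71%, however, and that sits badly with a 58% described as historic. Another near match, a one-sided test for a relative increase with 60 per arm (79.9%), conflicts with the two-sided rule of section 2.14 and points away from benefit. Reading 100 as the number per arm, with continuity correction, gives 35.6% relative, but that would confuse the total with the arm size.

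It can also be said that the figure is a side remark. That stands: the trial's size comes only from the transfusion outcome, which reproduces.

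A reader might infer that a null result on the composite is going to be taken as excluding an important effect. The protocol says nothing of the kind; such a result would be judged on its estimate and confidence interval. A reader might also treat this as the trial's leading safety and efficacy endpoint. The protocol calls it only a secondary composite. Nor is it a fault that section 2.7 does not list the composite by name: its components are listed there and section 2.8 names it.

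Finally, 50 per arm is not the obvious n for this outcome, since deaths are one reason for the drop from 120 to 100 and death is part of the composite. That is fair, and it makes 60 per group the more natural basis.

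**Conclusion.** The point holds in a limited form. With 58% as the standard-care rate, 1:1 allocation, two-sided 0.05 and 50 or 60 infants per arm, a 36% difference does not correspond to 80% power on either scale: the power is about 97% to 99% if the 36% is absolute and about 55% to 63% if it is relative. The choice of test formula does not explain the gap. The conclusion rests on reading the historic 58% as the control rate, which is the natural reading but is not stated.

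The severity is minor to moderate. A detectable difference for a secondary outcome is misstated or insufficiently defined; the sample size, the randomisation and the primary analysis are not affected.

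**What to change.** Replace the sentence in section 2.8 with one that states the scale, the n and the reference arm. If 58% is the control rate, it could read: with 58% in the control group and 60 infants per group, the trial has 80% power (two-sided 0.05) to detect an absolute fall of about 25 points, to about 33% (relative reduction 43%); if only 50 per group can be assessed, about 28 points, to about 30.5% (relative 47%). If the authors meant 58% as the average over both arms, they should say so and give the control rate of about 71% that this implies, with its source.

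The cost is one sentence. If the 36% was meant as relative, the corrected figure will be less favourable than the one now printed. Nothing else in the design has to change.
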